**Quality assessment of the specimens**		
**Adverse effects**		
	**Unadjusted Coef (CI)*****P***	**Adjusted Coef (CI)*****P***
**Patient experience**		
Five-point Likert scale		Sub-analyses
To assess agreement between forced expiratory technique alone and induced sputum combined with the forced expiratory technique, a kappa statistic will be calculated [48].If the kappa statistic indicates a lack of agreement between forced expiratory techniques [50], a sensitivity analysis comparing forced expiratory technique with tracheal suction and induced sputum with tracheal suction will be utilized. A hierarchical mixed effect logistic model will be utilized for both analyses.For patients where expectorate cannot be obtained in the intervention group, descriptive analyses will be conducted on the numbers of tracheal suctions performed and the obtained specimen quality.Kappa statistics will be performed to identify differential quality criteria of Gram stain results classified in three groups (Table 3). Bacterial pathogens are described in Table 4.

**Table 3 Tab3:** Gram stain results classified according to the number of epithelial cells and polymorphonuclear leucocytes judged by microscopy (100× magnification)

Epithelial cells	Polymorphonuclear leucocytes		
	< 10	10–24	≥ 25
≥ 25			
10–24			
< 10

**Table 4 Tab4:** Bacterial pathogens identified in culture according to differential quality criteria. Results are presented in percentages

	Squamous cells < 10	Squamous cells 10–24	Squamous cells ≥ 25

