### Baseline variables {25}

Demographics, symptoms, and smoking are collected from a patient interview. Vital parameters, comorbidities, suspicion of pneumonia, diagnostic packages [33], severe acute respiratory syndrome coronavirus 2 (SARS-CoV-2), disease severity assessment (CURB-65 [34], PSI [35], and Danish Emergency Process Triage (DEPT) [36]), blood tests (C-reactive protein, leucocytes, neutrophils) length of hospital stay, antibiotic consumption, and inhaled medicine are extracted from the patient’s medical record (Table 1).

**Table 1 Tab1:** Demographic and baseline clinical characteristics

Variable	Overall	Group 1 total (*n* =)	Group 2 total (*n* =)
		Tracheal suction (*n* =)	Forced expiratory technique (*n* =), induced sputum (n =)
Site			
Aabenraa			
Sønderborg			
Sex, *n* (%)			
Age, mean (SD)			
Smoking status			
Current smokers, *n* (%)			
Ex-smokers, *n* (%)			
Non-smokers, *n* (%)			
Symptoms			
Cough, *n* (%)			
Expectoration, *n* (%)			
Chest tightness, *n* (%)			
Dyspnea, *n* (%)			
Severity assessment			
CURB-65 score* 0–1, *n* (%)			
CURB-65 score* 2, *n* (%)			
CURB-65 score* 3–5, *n* (%)			
PSI* risk class 2–3, *n* (%)			
PSI* risk class 4, *n* (%)			
PSI* risk class 5, n (%)			
Triage level 1, *n* (%)			
Triage level 2–3, *n* (%)			
Triage level 4–5, *n* (%)			
Diagnostic packages			
Airways symptoms, *n* (%)			
Fever, *n* (%)			
Dyspnea, *n* (%)			
Unspecific illness, *n* (%)			
Suspicion of COVID-19 infection, *n* (%)			
Other, *n* (%)			
Suspicion of pneumonia, *n* (%)			
SARS-COV-2 positive at admission, *n* (%)			
Comorbidities			
COPD*, *n* (%)			
Asthma, *n* (%)			
DM*, *n* (%)			
CVD*, *n* (%)			
Cancer, *n* (%)			
Other, *n* (%)			
Vital parameters			
SaO_2_*, mean (SD)			
RR*, median (IQR)			
HR*, median (IQR)			
Systolic blood pressure, median (IQR)			
Diastolic blood pressure, median (IQR)			
Fever > 38 °C, *n* (%)			
Altered mental status, *n* (%)			
Blood tests			
C-reactive protein, mean (SD)			
Leucocytes, mean (SD)			
Neutrophils, mean (SD)			
Did the patient receive antibiotic treatment			
Within 1 month, *n* (%)			
Before sputum collection, *n* (%)			
Inhaled medications, *n* (%)			
Length of hospital stay, mean (SD)			

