## Statistical method

### Sample size consideration {11}

It is hypothesized that the intervention group receiving expiratory techniques is non-inferior to the tracheal suction group. Grouping two methods in the intervention arm, there will be fewer missing values and only two comparison groups.

Based on clinical practice and literature, it is assumed that no sample will be obtained from 50% of patients by forced expiratory technique alone [9, 10, 42], 30% from patients by sputum induction combined with the forced expiratory technique [23, 43], and 10% from patients using tracheal suction [28]. The proportion of obtained samples classified as good quality is assumed to be 75% for the procedures using expiratory techniques [23, 27, 43] and 90% for tracheal suction [28].

Considering these assumptions, the study’s power is 84% with 260 patients, including missing values. The power of the study was calculated with a Monte Carlo simulation using logistic regression.

An internal register showed that at least 1250 patients were admitted to the study ED with suspicion of infection annually, and of these, 600 patients were diagnosed with pneumonia. Including 260 patients with suspected LRTI will take five months, taking into account exclusion criteria, weekends/holidays, and missing data.

To avoid overfitting in the primary analysis, we followed the relaxed one in ten rule for the fixed effects and one in 20 rule for the random effects [44].

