#### Definition of analyses population {20}

The primary analysis will be conducted according to the intention-to-treat (ITT) principle [46, 47].

We define the ITT population as all admitted patients suspected of LRTI who sign informed consent and subsequently are allocate to one of two sputum collection groups. Sputum samples obtained by tracheal suction from patients in the intervention group, who are not able to expectorate, will be analyzed separately from the ITT analyses.

The primary analysis compares the tracheal suction group and the expiratory technique group to identify the most effective method for obtaining good quality sputum samples. The secondary analysis consists of an agreement analysis [48] between forced expiratory technique alone and forced expiratory technique after sputum induction.

Additionally, analysis of the secondary outcome of adverse effects will be conducted at baseline (right after allocation) and at the latest, 10 min. after the intervention. Clinical symptoms (cough, expectoration, chest pain, or dyspnea), SaO_2_, RR, and CR10 Borg scale [40] will be measured. Furthermore, a 5-point Likert scale will be used to measure patient experience of the procedure. The analyses will be adjusted for variables with a large influence on the outcome, which is an odds ratio larger than 2, to accommodate bias [49].

Descriptive analyses will be performed on the pathogens found when the specimens are cultured according to differential quality criteria.

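### The planned kappa between forced expiration alone and induced sputum has no described pairs to work on, and even with pairs it would be the wrong trigger for the technique-specific comparisons

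*SAP article*

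**What the plan says.** Under *Analysis for primary outcome*, Sub-analyses, the SAP plans: "To assess agreement between forced expiratory technique alone and induced sputum combined with the forced expiratory technique, a kappa statistic will be calculated". *Definition of analyses population {20}* gives the same step more weight: "The secondary analysis consists of an agreement analysis" of these two techniques.

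The result decides what follows. "If the kappa statistic indicates a lack of agreement between forced expiratory techniques", then "a sensitivity analysis comparing forced expiratory technique with tracheal suction and induced sputum with tracheal suction will be utilized", each by a hierarchical mixed logistic model. The text itself gives no cut-off for lack of agreement, although it cites a reference at that point.

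Three places bear on whether any patient has a sample by both techniques:
- Table 1 has one intervention column, whose header carries two counts: "Forced expiratory technique (*n* =), induced sputum (n" and so on.
- *Sample size consideration {11}* pools the techniques partly to reduce missing values. It assumes that "no sample will be obtained from 50% of patients by forced expiratory technique alone", and that this falls to 30% when induction is combined with forced expiration.
- *Randomization {10}* sends intervention patients who deliver no specimen to tracheal suction. It does not mention a second expiratory sample.

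**The concern.** Kappa measures agreement between two ratings of the same unit. Here the unit would have to be a patient with one sample from the forced expiratory technique (FET) alone and another after saline induction, each classed as suitable or not. The SAP nowhere plans two expiratory samples from one patient, and its yield assumptions read most naturally as induction being used after FET has failed.

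This kappa is the only check on pooling the two techniques that the plan sets out. If it cannot be computed, the analyst must either skip the technique-specific comparisons or improvise a rule after seeing the data, which the SAP's Discussion says the plan exists to prevent. If it can be computed on some patients, the question is whether it answers what the trigger needs to know: do the two techniques give the same proportion of suitable samples?

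**Working it through.** **1. The plan's own figure.** The SAP gives no figure for the kappa. The only related one is 84% power with 260 patients, which uses the same yields. Inputs: 130 per arm (1:1), suction 90% obtained and 90% suitable, expiratory 75% suitable, two-sided 5% (sidedness is assumed). The 30% without a sample can be read in two ways:
- A: 30% of those who fail FET. Obtained 50% + 0.70 × 50% = 85%, or 110.5 samples.
- B: 30% of the whole arm. Obtained 70%, or 91 samples.

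Suction gives 130 × 0.90 = 117 samples. Power = Φ[(0.15 − 1.96·SE0)/SE1], with SE0 from the pooled proportion and SE1 from the separate ones.
- A: SE0 = 0.0502, SE1 = 0.0497, power 85.1%.
- B: SE0 = 0.0520, SE1 = 0.0532, power 81.7%.

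Simulating a two-group logistic model without random effects gives 85.6% (A) and 82.0% (B) by Wald test, and 86.3% and 82.6% by likelihood ratio. The stated 84% lies between the two readings and does not settle which was meant, so both are carried forward.

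**2. How many pairs?**
- Induction only after failed FET: 65 patients (130 × 0.50) give an FET sample. Others give an induced one: 65 × 0.70 = 45.5 (A) or 91 − 65 = 26 (B). Pairs: 0, by construction.
- Both techniques tried in every intervention patient, with yields of 50% and 70%: pairs lie between 130 × (0.50 + 0.70 − 1) = 26 and 130 × 0.50 = 65.

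The yields alone therefore do not fix the number of pairs; the order of the procedures does, and the SAP text does not state it.

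**3. What would kappa show if pairs existed?** Let both techniques give 75% suitable, as the plan assumes. Chance agreement is 0.75² + 0.25² = 0.625, and kappa = (observed agreement − 0.625)/0.375.
- Least overlap (both suitable in 50%): observed 0.50, kappa = −0.33.
- Independence (56.25%): observed 0.625, kappa = 0.
- Full overlap (75%): observed 1.00, kappa = 1.00.

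Now let the proportions differ by 15 points, 75% and 90%, with the greatest overlap. Observed agreement is 0.75 + 0.10 = 0.85, chance agreement is 0.675 + 0.025 = 0.70, and kappa = 0.15/0.30 = 0.50. So two techniques with equal proportions can have kappa 0, while two that differ by 15 points can have kappa 0.50. The ordering can run opposite to the question asked.

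**4. Precision of the comparisons behind the trigger** (sequential reading, 117 suction samples at 90%, expiratory at 75%). Half-width = 1.96·√(0.75·0.25/n + 0.90·0.10/117):
- FET alone, n = 65: 11.8 points.
- Induced, n = 45.5 (A): 13.7 points (13.8 with n = 45).
- Induced, n = 26 (B): 17.5 points.

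For FET against induced within the arm, 1.96·√(0.1875·(1/65 + 1/n)) gives 16.4 points (n = 45.5) and 19.7 points (n = 26). The Abstract gives 280 patients instead of 260; that multiplies every half-width by √(260/280) = 0.964.

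**The case against.** The strongest reply is that the SAP never says induction follows only failed FET. The two procedures are described separately, each ending with a stored sample, and neither excludes the other. Figure 1 may show the sequence, but it is not available here, and planning an agreement analysis is itself some sign that paired samples were foreseen. Table 1 shows two counts in one column header; it does not say that they are mutually exclusive. All of this stands. A reader might infer that no patient can have both samples, so that the kappa is certainly impossible. The documents support that only as the likelier reading. Zero pairs is a consequence of assuming sequential use; it does not follow from the yields.

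A reader might also infer that the induced-versus-suction comparison is necessarily less precise than the 15-point difference named under *Adherence and protocol deviations {19}*. That holds for 26 induced samples (17.5 points) but not for 45 (13.8 points).

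Finally, these are sub-analyses, and the SAP does not claim that the technique-specific comparisons are randomised. That is fair, and it limits the consequences. It does not rescue the trigger, because step 3 of the working holds however many pairs there are. Any pairs would also come only from patients able to expectorate both ways.

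**Conclusion.** The point holds in two branches. If induction is used only after FET yields nothing, there are no pairs and the kappa cannot be estimated. If some patients give both samples, the kappa can be computed but measures within-patient concordance, which does not show whether the techniques give equal proportions of suitable samples or compare equally with suction. On either branch it is the wrong check on pooling and the wrong trigger.

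The comparisons behind the trigger also need a plainer label than sensitivity analysis. Their subgroups form after randomisation, apparently by ability to expectorate, and are set against a suction arm without matching selection. On the plan's yields, about 65 FET and 26 to 45 induced samples are expected. The half-width for induced sputum against suction is then about 14 to 17.5 points, depending on how the 30% is read. These counts assume 130 per arm and sequential use.

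The pooled primary comparison does not depend on this kappa. The separate kappa on Gram-stain quality criteria is not in question, since two criteria can be applied to one specimen.

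**What to change.** Remove this kappa and the condition attached to it, in both sections where it appears. In its place:
- State in the text whether induction follows only an unsuccessful FET attempt or whether some patients give both samples. If pairs were intended, give the expected number and the question they answer.
- Always report, within the intervention arm, how many patients fall at each step (sample by FET alone, sample after induction, no sample). For the first two, give the proportion suitable with a 95% CI, and add the unpaired risk difference between them with its 95% CI. Describe this as non-randomised.
- If the technique-versus-suction models are kept, run them regardless of any preliminary result and label them exploratory and non-randomised, because the subgroups are formed after allocation.

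This changes SAP wording only. It needs no further patients and no data beyond a record of which technique produced each sample, which the two counts in Table 1 already require.

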**Bacterial agents**			
*Streptococcus pneumonia*			
*Haemophilus influenza*			
*Moraxella catarrhalis*			
*Pseudomonas aeruginosa*			
*Staphylococcus aureus*			
*Enterobacteriaceae*			
*Hemolytic streptococci*			
Pharyngeal flora			
No growth of pathogens			
Others			

#### Analysis for secondary outcomes

For the secondary outcomes regarding adverse events and patient experience, the following analyses will be utilized (Table 2):
To investigate if the number of adverse events differs between groups, a mixed effect Poisson model will be utilized with and without imputed values to accommodate the random effect’s hierarchical structure, which manifests according to different personnel collecting the samples and geographical variation.
A sensitivity analysis for each adverse event type by either a chi-square test or Fischer’s exact test will be performed (Table 5).

**Table 5 Tab5:** Sensitivity analyses for adverse events

Adverse events	Expiratory techniques, ***n*** (%)	Tracheal suction, ***n*** (%)	***P***

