C*oughing, expectoration, dyspnea, and chest pain* symptoms will be reported as binary variables. Aggravation of cough, expectoration, dyspnea, and chest pain experienced by the patient will be reported.*Oxygen saturation.* Oxygen saturation (SaO_2_) will be measured using a pulse oximetry device to measure arterial oxygen saturation level in percentages up to 100%. The acceptable SaO_2_ is ≥ 93%. For patients with chronic obstructive disease, a SaO_2_ is acceptable at ≥ 88%. SaO_2_ will be reported as mean (standard deviation (SD)) [37].*Respiratory rate.* The respiratory rate (RR) will be counted by the professional attending the patient. The respiratory rate is the number of breaths per minute that a patient takes while resting. It is assessed by counting the number of times the patient’s chest rises in half a minute multiplied by two. RR will be reported as mean with standard deviation (SD). Acceptable results for RR are between 12 and 20 times per minute [38].*Side effects observed by the project assistants.* Project assistants will register any side effects such as bleeding from the airways and bronchospasm.*Short-term mortality.* Mortality within 7 days from admission to the emergency department*Re-admission.* Re-admission to hospital within 30 days of the original discharge*Patient’s overall experience of symptoms.* Patient wellbeing and overall experience of symptoms will be measured at the latest 10 min after sputum collection. Patients will asked to verbally score their overall experience of their symptoms based on the CR10 Borg scale [39, 40]. The CR10 Borg scale assess the experience of patient symptoms ranges from “0= nothing at all” to “10 very very strong” and over 10 as “maximal” [40]. A visual support tool describing this scoring system will be used to assist the patient and the ordinal result will be reported as mean and SD.*Patient’s experience of the procedure to collect sputum sample*: This will be measured once after an attempt at sputum collection. Patients will be asked to give a verbal score to the question: “What was your experience of this procedure?” using a five-point Likert scale. This scale ranges from “very bad, bad, neither bad nor good, good, very good”. A visual support tool describing this scoring system will be used to assist the patient. The result will be reported in percentages. The development and validation of this scale was based on individual and focus group interviews using cognitive interview methods [41].

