#### Confidence interval and *p*-value {16+17+18}

For the main analysis and the supplementary analysis with non-ordinal outcomes, 95% confidence intervals will be reported. For the supplementary analysis of the secondary outcomes, bootstrapped confidence intervals will be calculated for ordinal outcomes to accommodate lack of fit. A *p*-value less than 0.05 will be considered statistically significant.

No adjusting for multiple testing will be utilized in any analyses, as we only have one primary outcome [45].

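### SaO2, respiratory rate and Borg score are measured before and after collection, but the only per-measure arm comparison specified is a test on a yes/no event, with no effect estimate or interval

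*SAP article*

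**What the plan says.** All references are to the SAP article.

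- **Measurement.** Under Co-variables and Definition of analyses population {20}, SaO2, RR and the Borg score are taken right after allocation and again within 10 minutes of the procedure. Co-variables says that these measures will be compared between the groups and summarised as mean and SD, but names no method for the comparison.
- **Events.** Outcome definitions {26} makes each one binary. SaO2 and RR count when they worsen and lie outside a stated limit. Borg counts when it worsens.
- **Main harms analysis.** Analysis for secondary outcomes fits a mixed-effect Poisson model to the number of adverse events. That number also includes symptoms, observed side effects, death within 7 days and re-admission within 30 days. Table 2 reports it with an interval.
- **Per-type analysis.** The same section adds "A sensitivity analysis for each adverse event type by either a chi-square test" or Fisher's exact test. Table 5 shows n (%) per arm and P.
- **Intervals.** Confidence interval and p-value {16+17+18} states: "For the main analysis and the supplementary analysis with non-ordinal outcomes, 95% confidence intervals will be reported". It provides bootstrapped intervals for ordinal outcomes and adds: "A *p*-value less than 0.05 will be considered statistically significant".

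**The concern.** The Background names hypoxia and desaturation as harms of tracheal suction, and a difference in adverse events is one of the trial's three objectives. Oxygenation and breathing are therefore the harms on which a reader will want an estimate. As planned, each gets a P value on a dichotomy. A patient whose saturation falls but stays above the limit contributes nothing, and a large fall counts the same as a one-point fall across the limit. A non-significant row then carries no upper bound on the difference, although the paired numeric readings that could supply one are already collected.

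**Working it through.** **1. Is a continuous comparison specified anywhere?**
- Descriptive statistics names the t-test and Wilcoxon test, but for baseline variables.
- The Wilcoxon test under secondary outcomes is for the Likert scale of procedure experience.
- The Poisson model uses the binary events, pooled.
- Co-variables promises a comparison without a model, an estimate or an interval.

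So none is specified for SaO2, RR or Borg. This rests on the text alone.

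**2. The plan's own power figure.** The plan states that "the study’s power is 84% with 260 patients, including missing values", for the primary outcome only. With 130 per arm and 10% and 30% without a sample, 130 × 0.90 = 117 and 130 × 0.70 = 91 are analysed. For 90% v 75% good quality the pooled rate is 0.834:
- SE under no difference = √(0.834 × 0.166 × (1/117 + 1/91)) = 0.0520
- SE under the alternative = √(0.09/117 + 0.1875/91) = 0.0532
- z = (0.15 − 1.96 × 0.0520)/0.0532 = 0.905, power 81.7%

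A Monte Carlo logistic model gives 82.1% (Wald) to 82.6% (likelihood ratio), within 2 points of 84%. No power is stated for any harm.

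**3. Inputs for the harms.** The plan gives no mean, SD or pre/post correlation for these measures, so all of these are assumptions. Common to every run: 130 per arm, two-sided 5%, shift in one arm only, COPD limit ignored, readings rounded (SaO2 to 1%, RR to 2/min).

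**4. One setting by hand.** SaO2 mean 95, SD 3, correlation 0.7, shift of half the SD of the within-patient change:
- Shift = 0.5 × 3 × √(2 × (1 − 0.7)) = 1.16 points
- Simulated event rates 18.5% v 34.0%, pooled 26.25%
- Chi-square: SEs 0.0546 and 0.0537; z = (0.155 − 1.96 × 0.0546)/0.0537 = 0.89; power 81%, so 19% missed (simulation 19%)
- Baseline-adjusted regression: SE = 3 × √(1 − 0.49) × √(2/130) = 0.266; z = 1.16/0.266 − 1.96 = 2.41; power 99%, so about 1% missed (simulation 1%)

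**5. The range, for a shift of half the SD of the change.** If that SD comes from reading noise and rounding alone, it is √(2σ² + 2 × step²/12):
- SaO2, σ 0.7–1.4: 1.07–2.02, so a shift of about 0.5–1.0 point
- RR, σ 1–2: 1.63–2.94, so a shift of about 0.8–1.5 breaths/min

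| Assumed baseline | Missed, chi-square | Missed, adjusted regression |
|---|---|---|
| SaO2 94.5 (SD 2.5) | about 20–43% | 1–4% |
| RR 21 (SD 4.5) | about 22–41% | 1–6% |
| SaO2 96 (SD 2.5) | 36–63% | at most 5% |
| RR 18 (SD 4) | 56–69% | at most 5% |

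The spread in the first two rows partly reflects whether rounding is counted in the SD of the change. With bivariate normal readings and correlation 0.5–0.9, the chi-square test misses 7–85% (SaO2), 6–52% (RR) and 10–14% (Borg), against about 1–5%. The shifts there run from 0.5 × 2 × √0.2 = 0.45 to 0.5 × 3 × √1 = 1.5 SaO2 points.

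**6. Larger shifts.**
- With the first two baselines, the chi-square test misses 0–1% at 1.5 SaO2 points and 0–3% at 2 breaths/min.
- With half the SD of the measured value (correlation 0.5–0.9), it misses 0–12% for SaO2 mean 94–95, 0–13% for RR mean 18–24 and 0–10% for Borg.
- Away from the cut-offs the loss persists: 29–45% for SaO2 mean 97 (SD 2, shift 1 point) and 8–30% for RR mean 16 (SD 4, shift 2/min).

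**7. What P alone hides.** Suppose 2 v 7 bleeds among 130 per arm. P = 0.09 (chi-square) or 0.17 (Fisher). The risk difference is 5/130 = 3.8 points, with a Newcombe 95% CI of about −1 to +9.

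**The case against.** The per-type test is labelled a sensitivity analysis; the main harms analysis is the Poisson model, which has an interval in Table 2. Means and SDs will be reported, a group comparison is promised and intervals are promised in general terms. All of that is true, and a reader who infers that the continuous readings are discarded goes too far. What is absent is a specified arm comparison of them.

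A reader might also infer that this trial would miss a half-SD harm in SaO2 or RR 20–40% of the time. The documents do not support that. The figure needs means, SDs and noise that the plan does not give. It also applies to shifts at or below one recording step (1% and 2/min), whose relevance is debatable. With baselines near the cut-offs, somewhat larger shifts are detected almost always.

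Two further inferences fail. The plan nowhere says that P of 0.05 or more will be taken as equal safety; its non-inferiority hypothesis concerns obtaining samples. And low power for rare events such as bleeding (1% v 5%: 54% missed by chi-square, 68–70% by Fisher) reflects sample size. Bleeding is binary by nature, and an interval would bound the difference without raising power.

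The objection does not supply a per-measure estimate. A pooled count that includes death and re-admission cannot say whether saturation or breathing worsened, and a Table 5 without intervals does not deliver what the confidence interval section promises.

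**Conclusion.** The point holds as a gap in specification for secondary harm outcomes. For SaO2, RR and Borg the plan fixes only a dichotomised per-measure test, reported without estimate or interval, and this is at odds with its own statement on intervals. For small mean shifts the cost is roughly 20–60% of trials missed under plausible inputs (up to 69% in one setting, and 6–85% across all assumptions) against about 1–5% by baseline-adjusted regression. For shifts of about 1.5 SaO2 points or 2 breaths/min with baselines near the cut-offs, it is close to nil. These percentages depend on assumed means, SDs, correlations and reading noise, and are not properties of the plan. The missing estimate and interval do not depend on them.

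**What to change.** In Analysis for secondary outcomes and Table 5:

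- For SaO2 and RR, add the post-procedure value compared between arms with adjustment for its baseline value, reported as an adjusted mean difference with 95% CI.
- For Borg, add a baseline-adjusted ordinal or bootstrapped analysis with CI, in line with the plan's provision for ordinal outcomes.
- Keep the out-of-range events as clinical rows, and report every binary event type with a risk difference and 95% CI beside n (%) and P.

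The cost is SAP wording, a few extra model fits and some table rows, all on data already collected. The primary analysis and its conclusion do not change.
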